### Data collection

This study will use routinely collected patient care and health service reporting data. Sources will be: (1) the retrieval form, for clinical and timing information relating to the retrieval mission; (2) the patient chart, for diagnosis information and admission location at the tertiary hospital. For cases in the intervention arm, the audio and video of all consultations will be recorded to allow retrospective analysis. An activity log will be maintained to provide summary statistics of telemedicine and telephone usage during the study period.

Economic data routinely collected will include hospital admission data, length of stay by ward type, procedures, and Diagnostic Related Groups (DRGs). Additional data to be collected during the trial will include staffing, resource use and costs for the intervention, and the distance travelled by patients and their families. References for economic analyses will be: (1) The National Hospital Cost Data Collection Cost Report Round 14 (2009–2010) [25]; (2) current transport costs (sourced from emergency transport providers) and current (3) Queensland Health salary scales for staff costs.

### Sample size

In this study, resources limit the number of study sites to four and the study duration to 24 months. It is estimated that during the study period there will be 200 retrieval calls relating to eligible participants. We estimate an 80% participation rate (20% attrition due to lack of consent or clinicians electing not to consult by telemedicine and continuing by telephone) and consequently estimate the study will recruit a total of 160 retrieval participants with 80 in each arm. Retrospective stabilisation time data for the study sites showed a standard deviation of 41 minutes. With alpha = 0.05 we have 80% power to detect a clinically important difference in stabilisation time between-consultation types of 18 minutes or greater.

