#### Secondary outcome measures

Child’s physiological status using repeated measure scored using the Children’s Emergency Warning Tool (CEWT) (Authors: Royal Children’s Hospital, Queensland Health, unpublished) at two time points: (1) at time of initial call from the referring hospital (*CEWT*_*t*0_); and (2) at time of arrival of the retrieving team at the bedside at the referring hospital (*CEWT*_*t*2_).CEWT is an observation-chart based tool used within hospitals in Queensland. The tool is designed to identify patient deterioration and to trigger appropriate clinical escalations. The tool has nine components: respiratory rate, respiratory distress, Oxygen rate, Oxygen saturation, temperature, heart rate, blood pressure, capillary refill time, and level of consciousness. Observations are charted at the bedside, as with a conventional patient chart. Within each component, observations are translated to a score, on a scale of 1 (best) to 3 (worst). A score of ‘E’ and purple colour coding is used to prompt an emergency response (e.g. a respiratory rate <10 breaths/min, heart rate <60 beats/min or any component of blood pressure <50 mmHg).After each patient assessment, a total CEWT score is calculated by summing the component scores. A range of clinical responses are triggered by both significant negative changes in between-assessment component scores, and by the total CEWT score.Change in diagnosis (*DX*) using repeated measure taken at three time points: (1) at time of initial call to RSQ (*DX*_*t*0_); (2) at time of arrival of the retrieval team at the bedside at the referring hospital (*DX*_*t*2_); and (3) at time of arrival of the retrieval team and retrieved patient back at the PICU (*DX*_*t*5_).Destination of retrieved patients at the tertiary hospital (i.e. general ward vs. PICU).Retrieval decision (retrieval conducted/not conducted)PICU LoS for retrieved patients.

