### Data analysis

Data analysis will be conducted under the intention-to-treat (ITT) principle. Descriptive data will be presented as either mean (standard deviation) or median (25th to 75th percentile) for continuous data depending on its distribution, and as frequency (percentage) for categorical data. Statistical analyses for each outcome variable are shown in Table 2. All statistical analyses will be conducted using Stata (Statacorp, College Station).

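### The 80% power for 18 minutes counts a stabilisation time from every recruited child, and its 160 leaves out overridden children whom intention-to-treat would keep

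*Protocol article*

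**What the plan says.** All references are to the protocol article.

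- **Sample size.** From 200 eligible retrieval calls, 20% are taken off for two causes together: no consent, and clinicians who carry on by telephone instead of using telemedicine. The authors then "estimate the study will recruit a total of 160 retrieval participants with 80 in each arm". The variability input is given as "Retrospective stabilisation time data for the study sites showed a standard deviation of 41 minutes". The claim is that "we have 80% power to detect a clinically important difference in stabilisation time between-consultation types of 18 minutes or greater".
- **Primary outcome measure.** Stabilisation time is t3 minus t2, the retrieval team's time at the bedside in the referring hospital.
- **Secondary outcome measures and Table 2.** Whether a retrieval takes place is outcome S4, with its own logistic regression.
- **Hypotheses.** Telemedicine is expected to reduce the number of retrievals.
- **Randomisation and Patient recruitment.** Allocation is determined at the initial retrieval call. Clinicians may then override it for the child's sake, and such children are counted as cases lost to the study.
- **Data analysis.** "Data analysis will be conducted under the intention-to-treat (ITT) principle".

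**The concern.** The power statement uses the number recruited, but the primary analysis can use only children who have a stabilisation time. A child who is randomised at the call and then not retrieved has none. The protocol treats that result as possible, analyses it, and hopes telemedicine will make it more common. The only deductions shown are for non-consent and override.

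The second problem lies in the override deduction. Consent is sought before recruitment, so removing non-consenting families from the forecast is legitimate. An overridden child has already been allocated. Under intention-to-treat that child stays in the allocated arm and is not lost. The Patient recruitment and Sample size sections therefore conflict with the Data analysis section. In addition, the override described under Sample size (telephone used instead of telemedicine) can arise only among children allocated to telemedicine. With 1:1 allocation, removing them does not leave 80 in each arm.

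This is the only power statement for the primary outcome. If it is too favourable, readers of a null result will misjudge how likely the trial was to detect 18 minutes.

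**Working it through.** **Inputs from the documents:** SD 41 minutes; difference 18 minutes; 80 per arm; alpha 0.05 (sidedness not stated; two-sided reproduces the figure); 200 calls, 40 lost. **Not in the documents, so assumed below:** the fraction retrieved and the split of the 40 losses.

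**1. The plan's own figure.** Normal approximation, SE = 41 × √(2/80) = 6.48.
- Power = Φ(18/6.48 − 1.96) = Φ(0.817) = 79.3%.
- Detectable difference at 80% power = (1.96 + 0.8416) × 6.48 = 18.2 minutes.
- Number for a full 80% = 2 × (2.8016)² × 41²/18² = 81.4, so 82 per arm (164 in total).

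The stated figure reproduces to rounding, with nothing to spare.

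**2. Some children not retrieved (equal loss in both arms, full 18-minute effect).**

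| Retrieved (assumed) | Per arm | SE | Power | Detectable difference |
|---|---|---|---|---|
| 90% | 72 | 6.83 | 75.0% | 19.1 min |
| 80% | 64 | 7.25 | 70.0% | 20.3 min |

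**3. Overrides kept under intention-to-treat.** All are in the telemedicine arm, with no telemedicine effect in overridden children and everyone retrieved. If *o* of the 40 losses are overrides, N = 160 + *o*, n = N/2 per arm, and the mean effect is 18 × (1 − *o*/n).

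| Overrides (assumed) | n per arm | Mean effect | SE | Power |
|---|---|---|---|---|
| 10 | 85 | 15.9 min | 6.29 | 71.4% |
| 20 | 90 | 14.0 min | 6.11 | 63.0% |

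**4. Overrides dropped, as the 160 implies.** The arms are then n − *o* and n. With 10 overrides this is 75 v 85 and 79.1% power; with 20, 70 v 90 and 78.7%. At the outer limit, with all 40 losses being overrides, it is 60 v 100: SE = 41 × √(1/60 + 1/100) = 6.70 and power = Φ(0.729) = 76.7%.

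**5. What PIM3 adjustment could give back.** If 41 is an unadjusted SD, adjustment reduces it to 41 × √(1 − r²), where r is the correlation of PIM3 with stabilisation time. At 72 per arm, 80% power needs an SD of 38.5, so r ≈ 0.34. At 64 per arm it needs 36.3, so r ≈ 0.46. With 20 overrides kept (step 3) it needs 33.5, so r ≈ 0.58. The documents give no correlation.

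**The case against.** - **The sum is right, and overrides are not ignored.** Both points stand. A reader might infer that the protocol overlooked overrides, or that it does not expect the 160 to receive their allocated consultation. The documents do not support that: the 160 is already net of overrides. The fault is that the deduction conflicts with intention-to-treat.
- **The forecast may already consist of completed retrievals.** Study site selection reports 220 patients over two years at the four sites, ranked by retrieval activity. That is about 110 a year, against roughly 230 retrieved annually to the unit (110/230 = 48%). Advice-only calls are also kept out of the trial. If the 200 come from that base, non-retrieval may be partly allowed for. This stands as a possibility, but the Sample size section speaks of calls and does not say. Even then, retrievals avoided through telemedicine would cost that arm stabilisation times.
- **18 minutes may mean the between-arm difference as randomised.** On that reading, keeping overrides increases N and improves detection: 2.8016 × 41 × √(2/85) = 17.6 minutes with 85 per arm. This also stands. The figures in step 3 apply to an 18-minute effect in children who actually receive telemedicine, with none in the others.
- **PIM3 adjustment may recover the loss.** It may, as step 5 shows, but the protocol claims no such gain.

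Assigning all 40 losses to override and keeping them would give 18 × (1 − 40/100) = 10.8 minutes and about 46% power. That figure should not be used, because the protocol names lack of consent as one cause of the losses.

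**Conclusion.** The point holds as a fault in how the power is stated. The 80% has no margin, it counts a stabilisation time from every recruited child, and its 160 comes from a deduction that the stated analysis principle does not allow.

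The size cannot be fixed from the documents. Before any PIM3 gain, and taking each source alone, power is about 75% to 70% with 90% to 80% retrieved. It is about 71% to 63% with 10 to 20 overrides kept and no effect in them. If overrides are dropped and everyone is retrieved, the loss of power is small (no lower than 76.7%), and the main cost is the departure from intention-to-treat.

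A reader might go further and say that the trial does not have the power it states, or that 80% is possible only with complete retrieval and adherence. The documents do not establish either, because the retrieval fraction, the override split, the origin of the 200 calls and the PIM3 correlation are all unstated. The conflict between the override deduction and intention-to-treat depends on no assumed rate.

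**What to change.** Revise the Sample size paragraph, and bring the Patient recruitment wording into line with it and with Data analysis:

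1. Split the 20% into non-consent and override.
2. State that overridden children stay in their randomised arm for analysis, and stop counting them as lost cases.
3. Say whether the 200 calls are completed retrievals. If not, give the expected retrieved fraction from the retrospective data.
4. Restate the power or the detectable difference for children with a stabilisation time under intention-to-treat. Say whether 18 minutes is the difference as randomised or the effect in children who receive telemedicine.
5. If a gain from PIM3 adjustment is relied on, state the assumed correlation and its source.

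The cost is a short rewrite and a less favourable stated power. No more patients and no change to the primary model are needed.

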### Data analysis

Data analysis will be conducted under the intention-to-treat (ITT) principle. Descriptive data will be presented as either mean (standard deviation) or median (25th to 75th percentile) for continuous data depending on its distribution, and as frequency (percentage) for categorical data. Statistical analyses for each outcome variable are shown in Table 2. All statistical analyses will be conducted using Stata (Statacorp, College Station).

**Table 2 Tab2:** **Statistical analyses for each outcome measure**

**Outcome measure**		**Statistical Method**
P1	Stabilisation time^1^	Linear regression with stabilisation time as the outcome, type of consultation as the main effect and PIM3 score as a co-variable
S1	Change in patient’s physiological status	Linear mixed effects model with physiological status as outcome, type of consultation and time as main effects, and a consultation-by-time interaction term.
S2	Change in diagnosis	Logistic mixed effects model with diagnosis as outcome, type of consultation and time as main effects, and a consultation-by-time interaction term.
S3	Destination of retrieved patients	Logistic regression with destination as outcome and type of consultation as the main effect.
S4	Retrieval decision	Logistic regression with retrieval decision as outcome and type of consultation as the main effect.
S5	PICU LoS^1^	Linear regression with LoS as the outcome, and type of consultation as the main effect.

^1^Data relating to stabilisation time and PICU LoS will transformed if necessary to meet assumptions of regression model.

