### Randomisation

Generation of intervention/control arm allocation sequences will occur centrally. Sequences will be generated using permuted block randomisation, with random block sizes of 6,8 or 10 entries and a 1:1 allocation ratio using an online true random number generation service [19]. The process of generating these sequences will be conducted by an independent party. Four tables of random numbers will be generated, one for each study site. Odd numbers will denote allocation to the control arm and even numbers to the intervention. The tables will be held securely on a server on a private network.

A password-protected custom application (accessible by computer or portable device), driven by the random number tables, will be provided for the PICU clinicians to determine cases and controls at time of initial retrieval call from RSQ. The application will record all accesses and allocations.

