### Patient recruitment

Patients will be recruited from the referring hospital paediatric wards, emergency departments or adult intensive care units.

Initial contact between the referring hospital clinician and RSQ will always be made by telephone (Figure 1). On receiving that call, the RSQ nurse co-ordinators, will then also contact the designated PICU consultant by telephone. Using the randomisation process, the PICU consultant will determine whether the consultation continues by telephone (usual care, control arm), or by telemedicine (intervention arm). While all parties will aim to comply with the study protocol, there may be circumstances under which the referring and PICU clinicians elect to override the randomisation process in the interest of the care of the child. The resulting loss of study cases will be monitored and recorded on a daily basis.

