**Retrieval process time points.**

#### Primary outcome measure

Stabilisation time (*ST*). Clinical time spent by the retrieval team with at the bedside at the referring hospital (*ST* = *time*_*t*3_ − *time*_*t*2_). We will analyse all participants after stratifying for initial risk, as measured using the Paediatric Index of Mortality 3 (PIM3) [14].

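### The primary model adjusts only for PIM3, although CEWT at the initial call is already collected before allocation and might add precision at almost no cost

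*Protocol article*

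**What the plan says.** In the protocol article, Table 2, row P1, the primary model is a linear regression of stabilisation time with "type of consultation as the main effect and PIM3 score as a co-variable". The section on the primary outcome measure presents PIM3 as the measure of initial risk and does not say when it is scored. A footnote to Table 2 allows stabilisation time to be transformed if the regression assumptions require it.

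The section on secondary outcome measures has CEWT scored twice, first "at time of initial call from the referring hospital" (t0) and again when the retrieval team reaches the bedside (t2). CEWT sums nine bedside items covering breathing, oxygen, temperature, circulation and consciousness, and it has a non-numeric E category for emergencies. In Table 2 it appears only as the outcome of S1.

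Under Randomisation, PICU clinicians use the allocation application "to determine cases and controls at time of initial retrieval call from RSQ". Under Patient recruitment, the referring hospital first telephones RSQ, RSQ then telephones the PICU consultant, and the consultant then obtains the allocation.

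The Sample size section says that resources cap the trial at four sites and 24 months. It goes on to "estimate the study will recruit a total of 160 retrieval participants with 80 in each arm" and states: "Retrospective stabilisation time data for the study sites showed a standard deviation of 41 minutes". It claims 80% power for an 18-minute difference at alpha 0.05.

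**The concern.** A baseline variable that predicts the outcome beyond the covariates already in the model reduces the residual variance, and with it the standard error of the treatment effect. CEWT at t0 is a candidate for three reasons.

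- It describes the child before allocation, so adjusting for it is legitimate.
- It measures bedside physiology, and the Discussion expects a child in better condition to be moved to definitive care more efficiently.
- It is already being collected.

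Recruitment cannot readily be extended, so precision from data in hand is worth having. A prespecified second severity covariate would also protect the single primary estimate against chance imbalance in physiology that PIM3 does not capture. In an open trial, such a choice is better made in advance than after the data are seen.

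**Working it through.** **1. Is CEWT at t0 a baseline value?** The CEWT text ties t0 to the referring hospital's first call, and the change-in-diagnosis text ties t0 to the first call to RSQ. Allocation happens at the later call from RSQ to the PICU consultant. On the text alone, t0 precedes allocation. Figure 2, which shows the time points, is not available, so this rests on the described call order. The t2 score comes after the consultation and cannot be used as a baseline covariate.

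**2. The plan's own figure.** Inputs from Sample size: n = 80 per arm, SD = 41 min, difference = 18 min, alpha = 0.05. The article does not say whether the test is two-sided; two-sided is assumed here.

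- SE = 41 × √(2/80) = 6.48 min
- Power ≈ Φ(18/6.48 − 1.960) = 79.3% (78.8% with the noncentral t)
- Difference detectable with 80% power = (1.960 + 0.842) × 6.48 = 18.2 min
- Required for a full 80%: 82 per arm, 164 in total, against 160 planned

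The stated 80% is reproduced within rounding. A one-sided test would give 87.1% and does not match.

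**3. Adding CEWT at t0.** Let r be the partial correlation of CEWT at t0 with stabilisation time, given PIM3. The article gives no value, so the range below is an assumption. So is treating 41 min as the SD left after PIM3. Then residual SD = 41 × √(1 − r²), and SE = residual SD × √(2/80).

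| Assumed r | Residual SD (min) | SE (min) | Power for 18 min | Detectable difference (min) |
|---|---|---|---|---|
| 0 | 41.00 | 6.48 | 79.3% | 18.2 |
| 0.1 | 40.79 | 6.45 | 79.7% | 18.1 |
| 0.2 | 40.17 | 6.35 | 80.9% | 17.8 |
| 0.3 | 39.11 | 6.18 | 82.9% | 17.3 |
| 0.4 | 37.58 | 5.94 | 85.8% | 16.7 |
| 0.5 | 35.51 | 5.61 | 89.4% | 15.7 |

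The gain over r = 0 is 0.4 points at r = 0.1, 1.6 at 0.2, 3.6 at 0.3 and 10.1 at 0.5.

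**4. If 41 min is the unadjusted SD.** The article describes it as the SD of retrospective data and mentions no adjustment. Suppose PIM3 correlates 0.3 with stabilisation time (an assumption). The planned model's residual SD is then 41 × √(1 − 0.09) = 39.11 min and its power is already 82.9%. A CEWT partial correlation of 0.3 on top raises this to 86.2%.

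**5. If fewer than 160 contribute.** Stabilisation time exists only for children who are retrieved, and whether retrieval takes place is itself outcome S4. If 90% contribute (72 per arm, an assumption), and 41 min is again the SD after PIM3, power is 75.0% without CEWT and 78.9% with it at r = 0.3.

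**The case against.** The strongest reply is that nothing here is wrong. Row P1 is a valid covariate-adjusted analysis with a prespecified measure of initial risk, and leaving out a second severity score biases nothing. That stands. The point concerns efficiency and not validity.

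Three stronger readings are tempting, and the article supports none of them.

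- *Precision is being thrown away.* This would require CEWT to predict stabilisation time beyond PIM3. No such correlation is given. Both are severity measures and may overlap heavily. At r of 0.2 or less the gain is under 2 power points, and the attractive figure at r = 0.5 has no support in the article.
- *The trial has no power margin.* That is true of the stated calculation only. If 41 min is unadjusted, any variance that PIM3 explains is margin that was not counted.
- *CEWT is the only free source of power.* Site is known for every child and has its own allocation sequence, and it is also absent from P1. A transformation under the Table 2 footnote might also change precision, and the minute-based figures above would then not carry over directly.

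It can also be said that CEWT is not ready to use as a covariate: the E category needs a number, and completeness in routinely collected data is unknown. Both are fair. However, S1 is a linear mixed model with CEWT as its outcome, so it needs the same scoring rule anyway, and a simple rule handles missing baseline values.

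Finally, covariates might be left to an analysis plan that is not shown. Table 2, however, states the covariate set for the primary model, so this is a choice that the article makes.

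**Conclusion.** The point holds as a possible, cheap gain in efficiency, not as an error and not as a demonstrated loss. P1 adjusts for PIM3 alone while a physiological score that precedes allocation is already collected. The omission leaves the treatment estimate unbiased.

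On the assumption that 41 min is the SD after PIM3, adding CEWT at t0 moves power from 79.3% to between 79.7% (r = 0.1) and 89.4% (r = 0.5). The gain is negligible at the low end and material from about r = 0.3. Where in that range the truth lies cannot be determined from the article. If PIM3 itself explains variance, the starting power is higher, but the direction of the change is the same. The conclusion also rests on the described call order placing t0 before allocation, and on a two-sided test.

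**What to change.** Before any outcome data are seen, change row P1 of Table 2 to: linear regression of stabilisation time on allocated arm, PIM3 and CEWT at t0. Add that:

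- the E category is scored by the same numeric rule as in S1;
- a missing CEWT at t0 is filled in by a simple rule that uses neither arm nor outcome, so that no child is dropped for want of a baseline value;
- the PIM3-only model is reported as a sensitivity analysis.

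The cost is one degree of freedom (with 160 children, residual degrees of freedom fall from 157 to 156), two short rules and one extra model. No new data are needed. If CEWT largely overlaps with PIM3, little is gained and almost nothing is lost.

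### The change-in-physiological-status analysis (S1) leaves the pre-randomisation CEWT score unadjusted, so it is valid but less precise than an analysis that adjusts for it

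*Protocol article*

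**What the plan says.** Table 2 of the protocol article, row S1, gives the method as a "Linear mixed effects model with physiological status as outcome, type of consultation and time as main effects, and a consultation-by-time interaction term". Nothing in the row adjusts for the first score or constrains the arms to a common mean at that point.

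Under Secondary outcome measures, CEWT is taken twice. The first score (t0) is "at time of initial call from the referring hospital". The second (t2) is "at time of arrival of the retrieving team at the bedside at the referring hospital".

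The order of events is given elsewhere in Methods/Design. Under Patient recruitment, the referring clinician telephones the retrieval co-ordination service first: "On receiving that call, the RSQ nurse co-ordinators, will then also contact the designated PICU consultant by telephone". Under Randomisation, the PICU clinicians use the allocation application "to determine cases and controls at time of initial retrieval call from RSQ". That section also provides a separate random-number table for each of the four sites, so site is a randomisation stratum.

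The hypothesis that S1 serves is the second one on clinical effectiveness: that telemedicine improves the child's condition between the first call and the team's arrival.

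**The concern.** The t0 score belongs to the moment of the referring hospital's call, and allocation comes one telephone call later. Randomisation therefore makes the expected arm difference at t0 zero. The S1 model nevertheless estimates that difference freely and subtracts it from the difference at t2. Whatever chance imbalance arises at t0 is carried in full into the treatment estimate, whereas a baseline-adjusted analysis subtracts only the part that predicts the later score.

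What is at stake is precision. S1 is the only listed analysis of whether the child is in better condition when the team arrives, and the article's Discussion presents a more stable patient as the route to faster evacuation. The Sample size section says that resources fix the trial at four sites and 24 months, so precision for S1 has to come from the analysis rather than from more children.

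**Working it through.** **The plan's own figure.** The article states power only for the primary outcome: 80 per arm, SD 41 minutes, difference 18 minutes, alpha 0.05 (taken as two-sided). The standard error is 41 × √(2/80) = 6.48 minutes, and 18/6.48 = 2.777. Power is Φ(2.777 − 1.960) = 79.3%, which agrees with the stated 80%. No SD, correlation or power is given for S1. Only the 80 per arm carries over.

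**Inputs for S1.**
- n = 80 per arm (Sample size section).
- Two time points, the first before allocation (Secondary outcome measures, Patient recruitment, Randomisation).
- rho, the correlation of CEWT at t0 and t2: not given; assumed 0.3, 0.5, 0.7 and 0.9.
- Effect of 0.4 SD: assumed, for illustration only.
- Equal variance σ² at both times and complete data: assumed.

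**Formulas.**
- Planned interaction (difference in mean change): variance = (2/n) · σ² · 2(1 − rho).
- Baseline-adjusted: variance = (2/n) · σ² · (1 − rho²).
- Ratio, adjusted to planned: (1 − rho²) / [2(1 − rho)] = (1 + rho)/2.

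**Results.** The effective number is 160 × (1 + rho)/2. Detectable differences are at 80% power, two-sided 5%, in SD units. Power is for 0.4 SD and equals Φ(0.4/SE − 1.960).

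| rho | adjusted variance as share of planned | reduction | effective N of 160 under the planned model | detectable difference, planned / adjusted | power, planned / adjusted |
|---|---|---|---|---|---|
| 0.3 | 0.65 | 35% | 104 | 0.524 / 0.423 | 57% / 76% |
| 0.5 | 0.75 | 25% | 120 | 0.443 / 0.384 | 72% / 83% |
| 0.7 | 0.85 | 15% | 136 | 0.343 / 0.316 | 90% / 94% |
| 0.9 | 0.95 | 5% | 152 | 0.198 / 0.193 | over 99% / over 99% |

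The rho = 0.5 power in full:
- Planned: SE = √(2/80 × 1.00) = 0.158; 0.4/0.158 = 2.530; Φ(0.570) = 72%.
- Adjusted: SE = √(2/80 × 0.75) = 0.137; 0.4/0.137 = 2.921; Φ(0.961) = 83%.

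Below rho = 0.5 the planned contrast is less precise than ignoring the baseline altogether, because 2(1 − rho) then exceeds 1.

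**Simulation.** With 80 per arm, 4,000 replicates and a true effect of −0.30, both estimators averaged about −0.30. The ratio of planned to adjusted variance was 1.55, 1.34 and 1.14 at rho 0.3, 0.5 and 0.7, close to the algebraic 2/(1 + rho) = 1.54, 1.33 and 1.18.

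**Unequal variances.** Let the SDs be s0 and s2. Planned minus adjusted variance, apart from the factor 2/n, is s0² + s2² − 2·rho·s0·s2 − s2²(1 − rho²) = (s0 − rho·s2)². This is never negative. The size of the gain depends on equal variances; its direction does not.

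**The case against.** The strongest reply is that nothing in row S1 is wrong. Arm, time and their interaction is a standard model, the interaction addresses the hypothesis, and the standard error already allows for chance imbalance at t0. All of that stands. A reader might infer that the planned test is biased or invalid; the simulation and the algebra show that it is neither.

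A second reply is that equal t0 means hold for all randomised children, not necessarily for those analysed. Patient recruitment foresees overrides and loss of cases. Attrition in the Sample size section includes clinicians staying with the telephone, which can arise only in the telemedicine arm. A t2 score also needs a team to arrive. This bears on the mixed model with a common t0 mean, which does assume equal means. It does not block the regression of the t2 score on arm and t0 score, which conditions on the baseline and does not require equal t0 means among the children analysed. Data analysis also states intention to treat. Selective loss would be a problem for the planned model too.

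A third reply is that the gain is unknown, since rho is not given, and at rho 0.9 it is only 5%. That stands, and is why a range is shown.

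A stronger reading is also tempting. The article says that "a total CEWT score is calculated by summing the component scores", while a score of E "and purple colour coding is used to prompt an emergency response" and is given no number. A reader might infer that the sickest children are mis-scored in S1. The article does not support this. It summarises an existing, unpublished hospital tool and leaves the numeric handling of E unstated, but it states no wrong rule. The tool, the full protocol or the SAP may supply one. Nor do the documents offer a basis for assigning E any particular number.

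**Conclusion.** The point holds as a loss of efficiency in one secondary outcome. CEWT at t0 is a pre-randomisation measurement, and the S1 model uses it as a raw subtraction instead of a covariate. Under equal variances and complete data, baseline adjustment cuts the variance by 35% to 5% for rho from 0.3 to 0.9. At rho 0.5 the planned test performs like an adjusted analysis of 120 children instead of 160.

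The move from about 72% to about 83% power rests on three things: 80 per arm with both scores, an effect of 0.4 SD and rho 0.5. The last two are assumptions. Children who are not retrieved have no t2 score; fewer children lower both power figures but leave the variance ratio unchanged. The validity of the planned model, the primary outcome and the scoring of E are not called into question. The change is worth making because it costs almost nothing and the sample cannot grow.

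**What to change.** In Table 2, row S1, make the main analysis a linear regression of CEWT at t2 on type of consultation, with CEWT at t0 and site (the randomisation stratum) as covariates. A mixed model with a common mean at t0, that is time and consultation-by-time without a consultation effect at t0, serves the same purpose and is equivalent when both scores are complete. Name one of the two as the main analysis in advance. Keep the planned interaction model as a sensitivity analysis.

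The cost is one table row. Both scores and site are already collected, and the extra covariates use a handful of degrees of freedom. The change should be fixed before any outcome data are examined by arm.
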